#### **10.1.5 Serious Adverse Events (SAEs)**

SAEs are those events recorded as “Serious” on the AE page of the eCRF. SAEs following the first vaccination to 364 days after the last vaccination will be summarized. Summaries will be produced of:

- Number of SAEs by treatment group, Medical Dictionary for Regulatory Activities (MedDRA) system organ class and preferred term
- Number of participants with SAEs by treatment group, system organ class and preferred term
- Number of participants with SAEs, assessed by investigator as possibly related to investigational product, by treatment group, system organ class and preferred term
- Number of participants with SAEs  $\geq x\%$  in either treatment group, by treatment and preferred term where x may be 1, 3 or 5

In the summary of number of participants, should a subject experience multiple events within a SOC or PT, the subject will be counted only once for that SOC or PT.

A listing of all SAEs including those prior to the first vaccination will be provided at the time of the primary analysis.

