| Vascular    | Thrombotic, thromboembolic, and neurovascular events: These are events that can manifest as transient or permanent vision problems, dizziness, trouble understanding, facial droop, slurred speech, unilateral weakness, deep vein thrombosis with swollen, warm or painful leg, pulmonary embolism with shortness of breath, chest pain or irregular heart rate                                                                                                                                                                                                                                                |
| Hematologic | Thrombocytopenia: Thrombocytopenia is a disorder in which there is an abnormally low platelet count; a normal platelet count ranges from 150 000 to 450 000 platelets per $\mu$ L.                                                                                                                                                                                                                                                                                                                                                                                                                              |
| Immunologic | Vasculitides: Vasculitides are a group of related disorders characterized by inflammation of blood vessels (vasculitis) leading to tissue or end-organ injury.                                                                                                                                                                                                                                                                                                                                                                                                                                                  |
|             | Anaphylaxis: Anaphylaxis an acute hypersensitivity reaction with multi-organ-system involvement that can present as, or rapidly progress to, a severe life-threatening reaction requiring immediate medical attention.                                                                                                                                                                                                                                                                                                                                                                                          |

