AESIs following the first vaccination to 364 days after the last vaccination will be summarized. The number and percentage of participants with AESIs will be summarized by treatment group, and by treatment, AESI term, and PT. Should a participant experience multiple events within a PT, the participant will be counted only once for that PT according to the first onset date.

A listing of all AESIs will be provided at the primary analysis.

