### 10.1.7 Death

Listings of all death due to causes other than COVID-19 will be provided at the time of the primary analysis.

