### 10.3 Subgroup Analysis

Overview of AEs including factors below will be summarized by subgroup.

- Incidence of all AEs
- Incidence of solicited AEs
- AEs by severity
- Incidence of unsolicited AEs
- Incidence of SAEs
- Incidence of AESI
- Deaths other than due to COVID-19

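### SAE and AESI totals by arm do not separate COVID-19, so where COVID-19 illness or its complications are recorded there, prevented disease can offset a non-COVID excess

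*SAP*

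**What the plan says.** SAP section 10.1.5 defines the events broadly: "SAEs are those events recorded as “Serious” on the AE page of the eCRF". On the window it states: "SAEs following the first vaccination to 364 days after the last vaccination will be summarized". The summaries are by arm. The displays include "Number of participants with SAEs by treatment group, system organ class and preferred term", an event count at the same level, a table of possibly related SAEs, a table above a frequency threshold, and a full listing at the primary analysis.

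Section 10.1.6 uses the same window: "AESIs following the first vaccination to 364 days after the last vaccination will be summarized". The display is: "The number and percentage of participants with AESIs will be summarized by treatment group, and by treatment, AESI term, and PT". Table 9 includes "Thrombotic, thromboembolic, and neurovascular events", other neurologic events and vaccine-associated enhanced respiratory disease (VAERD).

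The section 10.3 overview has undivided rows, among them "Incidence of SAEs" and a matching AESI row.

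Deaths are handled differently. Section 10.1.7 plans "Listings of all death due to causes other than COVID-19", and the death row in 10.3 also leaves out COVID-19 deaths. Hospitalised, severe, ICU-requiring and fatal COVID-19 are efficacy cases in Table 6.

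**The concern.** A serious COVID-19 episode is an efficacy event. If it is also entered as a serious AE, it counts in the harm tables. An effective vaccine makes such entries rarer in its own arm, so the difference in total SAEs becomes non-COVID harm minus prevented disease. The same can happen within a single AESI term. A pulmonary embolism during COVID-19 and one unrelated to infection fall under the same Table 9 concept.

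The plan accepts the need for separation for deaths and gives no reason for stopping there. At stake is how the SAE and AESI totals are read in a safety analysis written for a marketing application.

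**Working it through.** **The plan's own figures.** The SAP states no rate or power for SAEs or AESIs, so there is none to reproduce. The case counts used below come from section 4.1. Its power figures are approximately reproduced by an exact conditional binomial (1:1 allocation assumed, null efficacy 20%, stated two-sided alpha):
- 53 cases, VE 70%: power 77.4% (stated 77%); efficacy at the cut-off 64.1% (stated 64%).
- 105 cases, VE 60%: power 91.8%, or 88.5% by a Wald calculation on the log relative risk (stated 90%); efficacy at the cut-off 47.8% (stated 48%).

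**Deficit implied by the primary-analysis case count.**
- Vaccine share of cases = (1 - VE)/(2 - VE) = 0.4/1.4.
- Vaccine cases = 105 × 0.4/1.4 = 30; control cases = 105 - 30 = 75; difference = 45.
- Assumed share recorded as serious, equal in both arms: 5% gives 45 × 0.05 = 2.25; 10% gives 4.5; 20% gives 9.

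The deficit is therefore about 2-9 events. The 105 cases count only SD/SD recipients from 15 days after dose 2. The SAE tables count from dose 1, in all dose groups of the safety set, so the deficit there would be larger by an unknown amount.

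**Wider assumed range.** Table A2 gives about 19,800 participants for the any-dose safety set; a 1:1 split (assumed) gives 9,900 per arm. Deficit = 9,900 × control rate of serious COVID-19 × VE against it.
- Rate 0.1%, VE 60%: 9,900 × 0.001 × 0.6 = 5.9.
- Rate 0.2%, VE 80%: 9,900 × 0.002 × 0.8 = 15.8.
- Rate 0.5%, VE 90%: 9,900 × 0.005 × 0.9 = 44.6.

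**What one such deficit does to a total** (all rates assumed).
- Non-COVID SAEs, 0.5% in control: 9,900 × 0.005 = 49.5. With a true relative risk of 1.32, the vaccine arm has 65.3.
- Serious COVID-19: control 9,900 × 0.002 = 19.8; vaccine 19.8 × 0.2 = 4.0.
- All SAEs: control 49.5 + 19.8 = 69.3; vaccine 65.3 + 4.0 = 69.3; relative risk 1.00.

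**What the planned tables can recover.**
- An SAE coded to a COVID-19 preferred term has its own row, and event counts add up, so that row can be subtracted from the event total.
- A participant is counted once per class or term, so a participant total without COVID-19 cannot be rebuilt from term rows.
- A complication coded to another term is not recognisable as COVID-related in any table.
- The frequency table uses a threshold of 1%, 3% or 5%. At 1% of 9,900, a term needs 99 participants in an arm to appear.

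**The case against.** The strongest reply is that the SAP states nothing false. SAEs are split by class and term, full SAE and AESI listings are planned, possibly related SAEs have their own table, and the displays are descriptive, with no test or relative risk planned on the totals. Table A1 already plans severe, hospitalised, ICU and fatal COVID-19 from dose 1 in the any-dose set. Most of this stands, and it confines the problem to participant totals and shared terms. Two limits remain. A listing is not a comparison by arm. The any-dose efficacy set also restricts COV002 to four groups (about 19,200 participants against about 19,800 for safety), and its case definitions do not capture complications as adverse events.

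A reader might infer three stronger things that the document does not support:
- That COVID-19 admissions certainly enter the SAE tables. The SAP does not say whether COVID-19 episodes are entered on the AE page; the study protocols, not shown here, may. COVID-19 is also not itself a listed AESI.
- That a demonstrable harm would vanish. The magnitudes are assumed. A modest excess of 79 v 69 participants, for example, has relative risk 1.14 with SE of the log = √(1/79 + 1/69) = 0.165, so a 95% interval of about 0.83 to 1.58. That is compatible with chance before any COVID-19 event is added.
- That harm should be judged on COVID-excluded events. Exclusion conditions on a post-randomisation outcome that the vaccine changes. It would also remove VAERD, a named AESI that arises on infection, from the deciding row.

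**Conclusion.** The point holds in limited form. The SAE and AESI totals in 10.1.5, 10.1.6 and 10.3 carry no COVID-19 split, unlike deaths. To the extent that COVID-19 or its complications are recorded there, those totals and the terms shared with complications can understate a non-COVID excess. Term rows coded as COVID-19 and the listings resolve this only in part.

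The size is not known from the document. The plan's own case count gives a deficit of about 2-9 events if 5-20% of cases are serious, and more if counted from dose 1. The wider range of about 6-45 participants rests entirely on assumed rates and a 1:1 split. The effect is on interpretation; no planned test is affected.

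**What to change.** In 10.1.5, 10.1.6 and the 10.3 overview, keep the all-event SAE and AESI rows as the randomised comparison and add, by arm:
- (a) supplementary rows that leave out events coded to COVID-19 or occurring within a stated window after the adjudicated onset of a confirmed case;
- (b) a row for those COVID-19-associated events alone.

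State the window length in the SAP. State also that the three rows are read together, that harm is not judged on (a) alone, and that VAERD is always assessed from the all-event row and row (b).

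The cost is SAP wording and repeated table rows. Sections 4 and 9.1 already send all virologically positive cases to blinded adjudication, so no new data collection is needed. The downside is that the window is a convention and (a) conditions on a post-randomisation event, so (a) must stay supplementary.

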#### **10.1.6 Adverse Events of Special Interest**

AZD1222 AESIs are based on Brighton Collaboration case definitions ([SPEAC 2020](#)), clinical experience, and scientific interest. There is no current evidence to suggest that AZD1222 is associated with these AESIs.

**Table 9 Adverse Events of Special Interest**

| AESI        | Medical Concept                                                                                                                                                                                                                                                                                                                                                                                                                                                                                                                                                                                                 |
|-------------|-----------------------------------------------------------------------------------------------------------------------------------------------------------------------------------------------------------------------------------------------------------------------------------------------------------------------------------------------------------------------------------------------------------------------------------------------------------------------------------------------------------------------------------------------------------------------------------------------------------------|
| Neurologic  | Generalized convulsion: Seizures are episodes of neuronal hyperactivity most commonly resulting in sudden, involuntary muscular contractions. They may also manifest as sensory disturbances, autonomic dysfunction and behavioral abnormalities, and impairment or loss of consciousness.                                                                                                                                                                                                                                                                                                                      |
|             | Other neurologic events: These events would include new onset event (acute or subacute) motor and sensory disturbances (eg, weakness, numbness, paresthesias, hypoesthesia, hyperesthesia, dysesthesias), bowel/bladder dysfunction, gait impairment, or visual disturbance, or other sudden neurological deficit.                                                                                                                                                                                                                                                                                              |
| Vascular    | Thrombotic, thromboembolic, and neurovascular events: These are events that can manifest as transient or permanent vision problems, dizziness, trouble understanding, facial droop, slurred speech, unilateral weakness, deep vein thrombosis with swollen, warm or painful leg, pulmonary embolism with shortness of breath, chest pain or irregular heart rate                                                                                                                                                                                                                                                |
| Hematologic | Thrombocytopenia: Thrombocytopenia is a disorder in which there is an abnormally low platelet count; a normal platelet count ranges from 150 000 to 450 000 platelets per $\mu$ L.                                                                                                                                                                                                                                                                                                                                                                                                                              |
| Immunologic | Vasculitides: Vasculitides are a group of related disorders characterized by inflammation of blood vessels (vasculitis) leading to tissue or end-organ injury.                                                                                                                                                                                                                                                                                                                                                                                                                                                  |
|             | Anaphylaxis: Anaphylaxis an acute hypersensitivity reaction with multi-organ-system involvement that can present as, or rapidly progress to, a severe life-threatening reaction requiring immediate medical attention.                                                                                                                                                                                                                                                                                                                                                                                          |
|             | Vaccine-associated enhanced respiratory disease: The pathogenicity of VAERD has been linked to a vaccine immune response characterized by induction of non-neutralizing antibodies, and a T-cell response of the Th2 type with hypereosinophilia ( Lambert et al 2020 ). VAERD may manifest as a severe form of respiratory disease with prolonged fever, and diverse clinical manifestations of disease severity and pathological changes marked by increased areas of lung consolidation, broncho-interstitial pneumonia, and necrotizing bronchiolitis ( Rajão et al 2016 ). |
|             | 
Potential immune-mediated conditions: These conditions are a group of autoimmune inflammatory disorders characterized by an alteration in cellular homeostasis, which may or may not have an autoimmune aetiology. A list of events is provided below
 
 
• Gastrointestinal disorders 
 
○ Celiac disease
 
○ Crohn's disease
 
○ Ulcerative colitis
 
○ Ulcerative proctitis
 
 
 
                                                                                                        |

| AESI | Medical Concept                                                                                                                                                                                                                                                                                                                                                                                                                                                                                                                                                                                                                                                                                                                                                                                                                                                                                                                                                                                                                                                                                                                                                                                                                                         |
|------|---------------------------------------------------------------------------------------------------------------------------------------------------------------------------------------------------------------------------------------------------------------------------------------------------------------------------------------------------------------------------------------------------------------------------------------------------------------------------------------------------------------------------------------------------------------------------------------------------------------------------------------------------------------------------------------------------------------------------------------------------------------------------------------------------------------------------------------------------------------------------------------------------------------------------------------------------------------------------------------------------------------------------------------------------------------------------------------------------------------------------------------------------------------------------------------------------------------------------------------------------------|
|      | 
 
• Liver disorders 
 
○ Autoimmune cholangitis
 
○ Autoimmune hepatitis
 
○ Primary biliary cirrhosis
 
○ Primary sclerosing cholangitis
 
 
 
 
• Metabolic diseases 
 
○ Addison's disease
 
○ Autoimmune thyroiditis (including Hashimoto thyroiditis)
 
○ Diabetes mellitus type I
 
○ Grave's or Basedow's disease
 
 
 
 
• Musculoskeletal disorders 
 
○ Antisynthetase syndrome
 
○ Dermatomyositis
 
○ Juvenile chronic arthritis (including Still's disease)
 
○ Mixed connective tissue disorder
 
○ Polymyalgia rheumatic
 
○ Polymyositis
 
○ Psoriatic arthropathy
 
○ Relapsing polychondritis
 
○ Rheumatoid arthritis
 
○ Scleroderma, including diffuse systemic form and CREST syndrome
 
○ Spondyloarthritis, including ankylosing spondylitis, reactive arthritis (Reiter's Syndrome) and undifferentiated spondyloarthritis
 
○ Systemic lupus erythematosus
 
○ Systemic sclerosis
 
 
 
 |

| AESI | Medical Concept                                                                                                                                                                                                                                                                                                                                                                                                                                                                                                                                                                                                                                                                                                                                                                                                                                                                                                                                                                                                                                                                                                                                                                                                                                                                                                                                                                                                                                                                                                                                                                                                                                                                                                                                                                                                                                                                                                                                                                                                |
|------|----------------------------------------------------------------------------------------------------------------------------------------------------------------------------------------------------------------------------------------------------------------------------------------------------------------------------------------------------------------------------------------------------------------------------------------------------------------------------------------------------------------------------------------------------------------------------------------------------------------------------------------------------------------------------------------------------------------------------------------------------------------------------------------------------------------------------------------------------------------------------------------------------------------------------------------------------------------------------------------------------------------------------------------------------------------------------------------------------------------------------------------------------------------------------------------------------------------------------------------------------------------------------------------------------------------------------------------------------------------------------------------------------------------------------------------------------------------------------------------------------------------------------------------------------------------------------------------------------------------------------------------------------------------------------------------------------------------------------------------------------------------------------------------------------------------------------------------------------------------------------------------------------------------------------------------------------------------------------------------------------------------|
|      | 
 
• Neuroinflammatory disorders 
 
○ Acute disseminated encephalomyelitis, including site specific variants (eg, non-infectious encephalitis, encephalomyelitis, myelitis, radiculomyelitis)
 
○ Cranial nerve disorders, including paralyses/paresis (eg, Bell's palsy)
 
○ Guillain-Barré syndrome, including Miller Fisher syndrome and other variants
 
○ Immune-mediated peripheral neuropathies and plexopathies, including chronic inflammatory demyelinating polyneuropathy, multifocal motor neuropathy and polyneuropathies associated with monoclonal gammopathy
 
○ Multiple sclerosis
 
○ Neuromyelitis optica spectrum disorder
 
○ Narcolepsy
 
○ Optic neuritis
 
○ Transverse myelitis
 
○ Myasthenia gravis, including Eaton-Lambert syndrome
 
 
 
• Skin disorders 
 
○ Alopecia areata
 
○ Autoimmune bullous skin diseases, including pemphigus, pemphigoid and dermatitis herpetiformis
 
○ Cutaneous lupus erythematosus
 
○ Erythema nodosum
 
○ Morphoea
 
○ Lichen planus
 
○ Psoriasis
 
○ Rosacea
 
○ Sweet's syndrome
 
○ Vitiligo
 
 
 
• Vasculitides 
 
○ Large vessels vasculitis including: giant cell arteritis such as Takayasu's arteritis and temporal arteritis
 
○ Medium sized and/or small vessels vasculitis including: polyarteritis nodosa, Kawasaki's disease, microscopic polyangiitis, Wegener's granulomatosis, Churg– Strauss syndrome (allergic granulomatous angiitis), Buerger's disease, thromboangiitis obliterans, necrotizing vasculitis and anti-neutrophil cytoplasmic antibody (ANCA) positive vasculitis (type unspecified), Henoch-Schonlein purpura, Behcet's syndrome, leukocytoclastic vasculitis
 
 
 
 |

| AESI | Medical Concept                                                                                                                                                                                                                                                                                                                                                                                                                                                                                                                                                                                                                                                                                                                                               |
|------|---------------------------------------------------------------------------------------------------------------------------------------------------------------------------------------------------------------------------------------------------------------------------------------------------------------------------------------------------------------------------------------------------------------------------------------------------------------------------------------------------------------------------------------------------------------------------------------------------------------------------------------------------------------------------------------------------------------------------------------------------------------|
|      | 
 
• Other 
 
○ Antiphospholipid syndrome
 
○ Autoimmune hemolytic anemia
 
○ Autoimmune glomerulonephritis (including IgA nephropathy, glomerulonephritis rapidly progressive, membranous glomerulonephritis, membranoproliferative glomerulonephritis, and mesangioproliferative glomerulonephritis)
 
○ Autoimmune myocarditis/cardiomyopathy
 
○ Autoimmune thrombocytopenia
 
○ Goodpasture syndrome
 
○ Idiopathic pulmonary fibrosis
 
○ Pernicious anemia
 
○ Raynaud's phenomenon
 
○ Sarcoidosis
 
○ Sjögren's syndrome
 
○ Stevens-Johnson syndrome
 
○ Uveitis
 
 
 
 |

ADEM = acute disseminated encephalomyelitis; AESI = adverse event of special interest; GBS = Guillain-Barré syndrome; VAERD = vaccine-associated enhanced respiratory disease.

This list may be updated along with the studies.

AESIs following the first vaccination to 364 days after the last vaccination will be summarized. The number and percentage of participants with AESIs will be summarized by treatment group, and by treatment, AESI term, and PT. Should a participant experience multiple events within a PT, the participant will be counted only once for that PT according to the first onset date.

A listing of all AESIs will be provided at the primary analysis.

